#### Laboratory Session

Figure 1 shows the schematic procedure of data collection. It starts with a general preparation phase, where the baseline measurements of physiological parameters (hormones), control variables, and psychological variables (self-reports about well-being, stress experience, and motive-specific affect) take place. In the preparation phase for the TSST-G, the participants prepare for the task. The participants in the experimental group receive social support during this phase, while the participants in the control group do not receive any social support. Finally, there will be a 45-minute rest period during which repeated physiological and psychological questionnaires will be completed. A detailed procedure is provided in Multimedia Appendix 3.

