#### General Preparation Phase

In each laboratory session, 3 participants will arrive between 5:00 and 5:15 PM outside the laboratory and will be led individually to their own preparation room (so that they cannot contact each other). First, they will be asked to read the study information sheet again and then will provide their written consent (Multimedia Appendix 2). Afterwards, the participants will generate their participant code via paper and pencil format, which ensures that the saliva samples, as well as other collected data, can be stored anonymously. Then, they will complete a short day-screening questionnaire (Multimedia Appendix 4) on a computer, which will assess control variables (eg, sports, medication intake, smoking, and caffeine and alcohol consumption). Afterward, they will be asked to wear a pulse belt that contains a Polar H10 sensor (Polar Electro). When putting on the belt, the experimenter will leave the room. After that, the participants will provide an initial saliva sample at measurement time T0 (−11 min) and will complete the first test battery, including different questionnaires, on a computer (hereafter referred to as psychological questionnaires).

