### Test Battery of Psychological Questionnaires

Participants are asked to complete the psychological questionnaire a total of 7 times (Figure 1).

Well-being will be captured via 6 items (short version A) from the Multidimensional Well-Being Questionnaire (MDBF) [64]. The items start with “Right now I feel…” and will be continued with 1 of the following adjectives: good, bad, alertness, fatigue, relaxed, and restlessness. The participants will be able to rate them on a 5-level scale labelled from *not at all* to *very*. A slightly modified version of the trait anxiety scale of the State-Trait Anxiety Inventory [65] will be used to assess the momentary anxiety of the participants. A total of 6 adapted items are included, which can be answered on a 5-point scale, as follows: “How big do you think your fear is at the moment?”, “How much do you feel physically uncomfortable right now?”, “How strong is your need to leave the situation?”, “How tense is your feeling right now?”, “How much are you in control of the situation?”, and “How stressed do you feel?”. To our knowledge, no standardized motive-specific affect questionnaire exists so far. We therefore created an adjective list that is theoretically derived from early work by McClelland [19] and added adjectives that have been used in more recent research [66] (see the self-determination theory [67]). Participants indicated for 7 items how they feel right now by using a 7-point response scale (1, *not at all* to 7, *very much*). The items are “socially related,” “calm” (affiliation motive–specific affect; the item “relaxed” from the MDBF will also be used in the analysis for the affiliation motive), “strong,” “excited,” and “enthusiastic” (power motive), with “competent” and “self-determined” as additional items representing achievement and autonomy motive–specific affect, respectively (Multimedia Appendix 10). Construct validity of this motive-specific affect scale will be checked.

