### Statistical Analysis

Statistical analysis will be performed using IBM SPSS Statistics, Version 28 (IBM Corp) for Windows (statistical analysis and graphs). We will perform an analysis of variance with repeated measures to determine if the TSST procedure results in significant increases in psychological and biological variables for all participants. We will calculate multiple linear regressions to examine interaction effects. In these regressions, we will first include the control variables, then the condition as a dummy variable, and finally the individual predictors and their interaction terms. To account for repeated measurements of the collected hormones, the area under the curve with respect to increase will be calculated and used as a dependent variable [71]. As an additional effort to ensure that participants with a delayed significant increase in their hormones will not be excluded, an adjusted increase value will be calculated, regardless of the time of measurement. This value will be obtained by subtracting the baseline value from the peak value. Multiple regressions will be calculated again with these adjusted values. Nonbiological dependent variables, such as those obtained from the psychological test battery, will be added as means. Only data from individuals who have fully completed the TSST protocol will be included in the final analyses. Missing data will be added by multiple imputation.

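### The moderation regressions name no T0 covariate: hormones have T0 subtracted at full weight, and the self-report means do not say whether T0 is included

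*Protocol article*

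**What the plan says.** The Statistical Analysis section of the protocol article plans multiple linear regressions for the interaction effects. In these, "we will first include the control variables, then the condition as a dummy variable, and finally the individual predictors and their interaction terms".

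The outcomes are fixed as follows:
- Hormones: "the area under the curve with respect to increase will be calculated and used as a dependent variable".
- Hormones, second version: an adjusted increase, of which the article says "This value will be obtained by subtracting the baseline value from the peak value".
- Self-reports: "Nonbiological dependent variables, such as those obtained from the psychological test battery, will be added as means".

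On timing, Test Battery of Psychological Questionnaires states: "Participants are asked to complete the psychological questionnaire a total of 7 times". General Preparation Phase places the first of these at T0, where participants give an "initial saliva sample at measurement time T0 (−11 min) and will complete the first test battery". Support comes later, in the preparation phase of the stress test: "The participants in the experimental group receive social support during this phase". T0 is therefore measured before any support.

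On covariates, Statistical Analysis does not list the control variables. Study Design names gender role self-concept and unspecified others. Laboratory Session mentions baseline hormones, control variables and psychological variables as separate items. No section names the T0 value of an outcome as a covariate.

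**The concern.** A value measured before support carries no support effect but shares person-to-person variation with the later values. It can be ignored (coefficient 0), subtracted in full (coefficient 1), or entered as a covariate so that the data choose the coefficient. AUCi and peak minus baseline take the second route. A plain mean of later self-reports takes the first. A mean that includes T0 does worse, because it adds T0 in place of removing it and dilutes the effect.

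The covariate route is at least as efficient as either, apart from one degree of freedom. The tests affected are the condition by motive interactions of Hypotheses 2 and 3, which carry the study's main objective.

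**Working it through.** **Figures to reproduce.** There are none on this point. The article gives no correlation between time points, no variance, and no alpha, power or effect size, so absolute power for these tests cannot be derived. The check below is of relative efficiency.

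**Step 1: AUCi weights.** Times come from Salivary Cortisol and Reproductive Hormones, with the minute values from the procedure sections.
- Seven samples (-11, 0, 12, 20, 30, 45, 65 min): trapezoid weights 5.5, 11.5, 10, 9, 12.5, 17.5, 10; sum 76.
- Four samples (-11, 0, 20, 65 min): weights 5.5, 15.5, 32.5, 22.5; sum 76.
- AUCi subtracts T0 times the full 76 minutes, so the net weight on T0 is 5.5 - 76 = -70.5 in both schedules. The later samples together carry 76 - 5.5 = +70.5.

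Hence AUCi = 70.5 × (P - T0), where P is the weighted mean of the later samples. Regressing AUCi with T0 as a covariate gives the same interaction test as regressing P with T0 as a covariate, so AUCi need not be dropped.

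**Step 2: assumptions.** Unit variance at each time, the same correlation rho between any two times, and an effect of equal size at every time after T0.

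**Step 3: AUCi.** Let q be the sum of squared normalised weights in P.
- Seven samples: q = 875.75 / 70.5² = 0.176.
- Four samples: q = 1802.75 / 70.5² = 0.363.
- Var(P) = q + (1 - q)rho.
- Var(P - T0) = Var(P) + 1 - 2rho = (1 + q)(1 - rho).
- Residual variance with T0 as covariate = Var(P) - rho².
- Proportional cut = (1 - rho)² / [(1 + q)(1 - rho)] = (1 - rho)/(1 + q).

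Example at rho 0.5: 0.5/1.176 = 0.425 for cortisol; 0.5/1.363 = 0.367 for reproductive hormones.

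**Step 4: self-reports.** V6 = 1/6 + (5/6)rho is the variance of the T1-T6 mean, and V7 = 1/7 + (6/7)rho that of the seven-point mean. Efficiency relative to the T0-adjusted T1-T6 mean:
- T1-T6 mean, unadjusted: (V6 - rho²)/V6.
- Seven-point mean, unadjusted: (6/7)² × (V6 - rho²)/V7.

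Example at rho 0.5: V6 = 0.583, V7 = 0.571, V6 - rho² = 0.333. The results are 0.333/0.583 = 0.57 and 0.735 × 0.333/0.571 = 0.43.

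| rho | Variance cut, cortisol AUCi | Variance cut, reproductive AUCi | Efficiency, T1-T6 mean | Efficiency, mean including T0 |
|---|---|---|---|---|
| 0.3 | 60% | 51% | 78% | 60% |
| 0.5 | 43% | 37% | 57% | 43% |
| 0.7 | 26% | 22% | 35% | 26% |
| 0.9 | 9% | 7% | 12% | 9% |

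The cortisol AUCi loss and the T1-T6 mean loss move in opposite directions and meet near rho 0.5, at about 43% each.

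**Step 5: sensitivity.** If correlation instead decays exponentially with time (0.5/0.7/0.9 at a 15-minute lag), efficiency relative to T0 adjustment is 0.40/0.57/0.83 for cortisol AUCi, 0.87/0.69/0.31 for the T1-T6 mean and 0.70/0.54/0.23 for the seven-point mean. The pattern is the same.

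**Step 6: simulation of the interaction test.** 128 analysed participants (about 154/1.2), equal correlation, and an assumed slope on the standardised motive of +0.2 SD in one group and -0.2 SD in the other; 2,000 runs per setting. At rho 0.5, power for the T1-T6 mean rises from 81% to 96% with T0 as covariate, and for cortisol AUCi also from 81% to 96%. The seven-point mean has 70%. At rho 0.9, AUCi is at 99.95% or above either way, while the T1-T6 mean rises from 63% to 100%. These figures show the contrast; they are not the trial's power.

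Peak minus baseline was not quantified. It subtracts T0 with coefficient 1 as AUCi does.

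**The case against.** A reader might infer that T0 is averaged into the self-report outcome, since there are seven questionnaires and the outcome is a mean. The article does not say so. The sentence covers nonbiological outcomes in general, which would include speech performance, and that is rated from one interview on several items. Item means would fit both kinds of outcome. That objection stands, although item means alone would leave unstated how seven occasions become one regression outcome.

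Nor can a T0 covariate be ruled out. The control variables are not enumerated, and a full list is commonly left to a fuller document. This also stands in part: one can say only that T0 adjustment is not named, and that Laboratory Session lists baseline measures apart from control variables.

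Full-weight subtraction is what AUCi means. It is an established summary and suits hypotheses worded as increases. Nothing there is erroneous or biased, and the point is one of efficiency.

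Finally, rho is assumed, and for very stable hormones the gain is small. That is correct and limits the size claimed. It does not remove the point, because the regression finds the right coefficient without anyone having to know rho.

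**Conclusion.** The point holds as an efficiency improvement to outcomes that the article itself fixes. AUCi and peak minus baseline subtract one pre-support sample at full weight, the content of the self-report means is left open, and no T0 covariate is named.

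The possible gain ranges from slight to large. At rho 0.3 to 0.9 the variance cut is 60% down to 9% for cortisol AUCi and 51% down to 7% for reproductive hormones. The efficiency of an unadjusted T1-T6 self-report mean falls from 78% to 12%. These figures rest on equal correlation and a constant effect after T0, and each outcome will have its own rho.

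The documents do not support the broader claim that the plan wastes much of the power for Hypotheses 2 and 3. They give neither rho nor the inputs for absolute power, and the hormone and self-report losses peak at opposite ends of the range. A much worse self-report figure could be produced by supposing that the effect is confined to T1-T3, but much of that gap would come from the choice of time window and not from the handling of T0.

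**What to change.** In the first regression step, add the participant's T0 value of the outcome as a covariate, for AUCi, for peak minus baseline and for each self-report scale. Do the same for α-amylase if it is summarised in the same way. Keep AUCi.

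Define each self-report outcome as the mean over a stated set of time points after T0, excluding T0, and fix that set before the data are analysed (for example T1-T3 or T1-T6).

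The cost is two or three sentences and one degree of freedom per model. The T0 values are already being collected.

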### Explorative Statistical Analysis

There are exploratory analyses planned on the association of self-reported GRSCs with social motives and their moderating role in psychobiological responses to social support. No further subgroup analyses are planned.

### Monitoring

#### Data Monitoring

In addition to the 2 principal investigators, who are in constant communication about data, no other data monitoring committee is required.

#### Description of Interim Analysis and Stopping Guidelines

No interim analysis or guidelines for study termination are provided. Data collection will cease when the target sample size is reached.

#### Harms

No adverse side effects have been reported with the TSST protocol. The experimenters will collect spontaneously reported adverse events and ask participants at the end of the experiment explicitly whether adverse events or unintended effects occurred.

## Results

The Ethics Committee of the University of Constance approved the application to conduct the study on December 18, 2018. The start of the experiment was planned for the beginning of 2019 but was postponed to June 2021 due to COVID-19. The protocol version is dated May 22, 2022. Data collection will take place until the end of 2022. Publication of the initial results is planned for spring 2023.

## Discussion

The aim of this study is to investigate whether social motives and participants’ sex moderate the effect of social support in stressful situations. We expect that participants with a strong affiliation motive will benefit from social support in terms of reduced psychobiological stress responses when being critically evaluated by others. For those participants, social support is supposed to serve as a stress buffer. In contrast, social support is expected to act as a stress amplifier in participants with a high-power motive, resulting in higher psychobiological stress responses.

To elucidate the influence of implicit social motives on affect in specific situations, we will record participants’ motive-specific affect. We postulate that participants with a high affiliation motive, will respond to social support with affiliation and an increase in progesterone. Participants with a high power motive will show feelings of inferiority and a decrease in testosterone or estradiol.

To explore the influence of implicit motives without bias, we also consider sex as a variable in our study. It is hypothesized that males exhibit a higher power motive and females exhibit a higher affiliation motive. This is expected to be reflected in motive-specific hormones.

Some studies have shown that social support has positive effects [72], while others have reported no, small, or adverse effects of social support [73,74]. With the introduction of implicit motives as moderator variables, as well as taking sex into account, we strive to explain why people react differently in same situations. Through this person-situation approach, we enable a more differentiated view on the effect of social support in stress situations. In summary, with this sophisticated view, we aim to provide a foundation that interventions could be designed in an individualized way and therefore only produce positive effects and no adverse effects.

A broad investigation with induced stress, standardized social support, and the assessment of implicit motives has not been performed in any study known to us. Furthermore, we will cover a large spectrum of methods with our planned study. In addition to self-reports (psychological test battery) and ratings by third parties (ratings of speech performance), we will additionally assess a variety of physiological parameters (hormones, heart rate, and heart rate variability). Therefore, this study lays a comprehensive foundation for further gainful research.

The lack of a control group receiving no stress induction (placebo TSST) could be considered a limitation of the study. However, since the TSST is an established procedure that reliably elicits stress, we believe that a control group can be avoided for pragmatic reasons [51]. In addition, the participants, as well as the research team, will wear FFP2 masks throughout the experiment owing to COVID-19. The effect of mask wearing on the TSST is difficult to assess and will need to be observed.

## Appendix

Multimedia Appendix 1 Screening online survey.

Multimedia Appendix 2 Study information sheet for the laboratory session.

Multimedia Appendix 3 Study protocol.

Multimedia Appendix 4 Daily screening questionnaire.

Multimedia Appendix 5 Instructions for participants.

Multimedia Appendix 6 Social support instructions for the associate.

Multimedia Appendix 7 Procedure for the panel.

Multimedia Appendix 8 Manipulation check for social support.

Multimedia Appendix 9 Debriefing form.

Multimedia Appendix 10 Test battery of psychological questionnaires.

Multimedia Appendix 11 Instructions for the collection and processing of saliva samples.

Multimedia Appendix 12 Peer-review report by the Deutsche Forschungsgemeinschaft (German Research Foundation).

## Abbreviations

GRSC: Gender Role Self-Concept
MDBF: Multidimensional Well-Being Questionnaire
PSE: Picture Story Exercise
TSST: Trier Social Stress Test
TSST-G: Trier Social Stress Test for Groups
